### Diagnostic criteria

2.6

The participants must meet the following diagnostic criteria: patients with chronic obstructive pulmonary disease (COPD), acute respiratory distress syndrome (ARDS), or postoperative respiratory failure requiring mechanical ventilation. For the diagnosis of COPD, the guidelines for diagnosis and treatment of COPD (2013 Revised Edition) formulated by the Chronic Obstructive Pulmonary Disease Group of the respiratory branch of the Chinese Medical Association will be followed (Table 2).^[20]^ The diagnosis of acute exacerbation of chronic obstructive pulmonary disease (AECOPD) is completely dependent on clinical manifestations, that is, patients complain of sudden changes in symptoms (baseline dyspnea, cough, and/or expectoration) beyond the daily variation range^[21]^; ARDS will be diagnosed according to the 2012 ARDS Berlin diagnostic criteria (Table 3).^[22]^ Postoperative respiratory failure mainly refers to respiratory failure after surgery for central nervous system diseases. The diagnostic criteria for respiratory failure will be in accordance with the Internal Medicine (Eighth Edition), edited by Junbo Ge and Yongjian Xu.^[23]^

**Table 2 T2:** Diagnostic criteria for chronic obstructive pulmonary disease.

Clinical manifestation: Dyspnea, chronic cough, expectoration
Exposure history of risk factors: History of exposure to risk factors, such as smoking, occupational pollution, and biofuel exposure
Chest X-ray findings: Lung hyperinflation
Physical examination findings: Lung visual inspection: barrel chest; Auscultation: clear voice
Gold standard: Pulmonary function test: after inhalation of bronchodilator, FEV1/FVC < 70% was defined as persistent airflow limitation. COPD can be diagnosed after other diseases are excluded.

COPD = Chronic obstructive pulmonary disease, FEV1 = Forced expiratory volume in the first second, FVC = Forced vital capacity.

**Table 3 T3:** Western medicine diagnostic criteria for acute respiratory distress syndrome.

Onset time: Clear risk factors within 1 week of onset or new/acutely aggravated respiratory symptoms within 1 week.
Causes of pulmonary edema: Respiratory failure cannot be explained completely by cardiac failure or fluid overload; if there is no relevant risk factor, objective examination (such as Doppler echocardiography) is needed to eliminate pulmonary edema with increased hydrostatic pressure.
Chest-X-ray: There is decreased opacity in both lungs, which cannot be explained by education, lobular atelectasis, or nodular shadows.
Oxygenation status:
Light: When CPAP or PEEP ≥5 cmH_2_O, 200 mmHg < PaO_2_/FiO_2_ ≤ 300 mmHg
Moderate: When CPAP or PEEP ≥5 cmH_2_O, 100 mmHg <PaO_2_/FiO_2_ ≤ 200 mmHg
Severe: When CPAP or PEEP ≥5 cmH_2_O, PaO_2_/FiO_2_ ≤100 mmHg

CPAP = continuous positive airway pressure, FiO_2_ = inhaled oxygen concentration, PaO_2_ = partial arterial oxygen pressure, PEEP = positive end-expiratory pressure; if the altitude is higher than 100 m, the following correction formula can be used: [PaO_2_/FiO_2_ × local atmospheric pressure/760]. In patients with mild ARDS, noninvasive CPAP can be used.

### Qualification criteria

2.7

#### Inclusion criteria

2.7.1

Only patients who meet the following criteria will be included:

(1)Age ≥18 years.(2)Fulfillment of the diagnostic criteria of acute exacerbation of chronic obstructive pulmonary disease, acute respiratory distress syndrome, or postoperative respiratory failure requiring mechanical ventilation for ≥24 hours.(3)Clear consciousness and the ability to act in accordance with instructions.(4)Stable cardiopulmonary functions.(5)Voluntarily participation after signing an informed consent.

#### Exclusion criteria

2.7.2

The following patients will be excluded:

(1)Patients with rapidly progressive neuromuscular diseases(2)Patients with Acute Physiology and Chronic Health Evaluation II score >30 and expected to die within 48 hours(3)Patients with increased intracranial pressure, limb disability or loss, and unstable fracture(4)Patients included in other clinical trials

### Rejection, termination, and shedding criteria

2.8

All participants will be informed that they have the right to withdraw from the trial at any time and that they will receive standardized western medicine comprehensive treatment and ICU routine care regardless of participation. The reason for withdrawal will be recorded in their case report form (CRF).

All patients who do not meet the inclusion criteria will be excluded.

Patients who receive treatment but not in accordance to the regulations or those who have incomplete data will be excluded.

During the course of treatment, patients who withdraw voluntarily and those who experience adverse events (AEs) or serious AEs and not suitable for further treatment will be regarded as part of the attrition.

Patients with adverse reactions will be included in the statistics of adverse reactions. Patients who withdraw from more than 1/2 courses of treatment due to ineffectiveness will be included in the efficacy analysis.

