### Sample size

2.4

According to the preliminary clinical research data, the total effective rate of “improved sitting Wuqinxi” in preventing and treating common complications and adverse outcomes in mechanically ventilated patients was statistically different between the groups. The test level was α = 0.05. The test efficiency was 1 - β = 0.80. The sample size was estimated using G∗Power (version 3.1.2, Franz faul, Universitat kiwl, Germany), and the effect size was set as d = 0.50. After calculation, the number of participants needed in each group was 64, totaling to 128 participants. Considering an attrition rate of ≤20%, the total number of participants required for this study was calculated to be 160, with 80 participants in each group.

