#### Experimental group

3.1.2

The experimental group will receive the same treatment as the control group and will additionally be treated with the improved sitting Wuqinxi intervention.

(1)Establish the standardized flowchart of “improved sitting Wuqinxi”for mechanically ventilated ICU patients(2)There will be 3 groups of tiger opera at 09:00, 6 times in each group; 3 groups of bear play at 13:00, 6 times in each group; 3 groups of bird play at 15:00, 6 times in each group; and 3 groups of deer play at 19:00, 6 times in each group.(3)Establish the risk assessment system

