### Compliance

3.4

The researchers will pay close attention to patients’ compliance and exclude patients with poor compliance. The researchers will also pay attention to the daily vital signs and relevant safety indicators of each patient and immediately assess whether they can continue to participate in the study if AEs related to the intervention measures or other disease conditions arise, and take effective intervention measures for any adverse reactions.

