### Statistical analysis

3.7

Before analysis, the data of 2 participants with complete data will be carefully checked to ensure the accuracy of the data. All data will be analyzed by intention. SPSS version 22.0 (Chicago, IL) will be used to analyze the data. The measurement data will be represented as mean ± standard deviation. The paired t-test will be used to perform the before and after analyses of the same group. The chi-square test will be used for the counting data and the rank sum test will be used for grade data. The Kaplan–Meier method will be used for univariate analysis to explore each possible related factor. The multivariate Cox model will be used to adjust for variables with statistical significance (*P* < .05) in univariate analysis to detect the influence of these variables on the study measure outcomes.

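### Exclusions after randomisation for off-protocol treatment, incomplete data and poor compliance contradict the stated analysis by intention, and may bias the comparison, plausibly toward Wuqinxi

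*Protocol article*

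**What the plan says.** Four statements in the protocol article decide who is analysed.

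- Section 3.7 (Statistical analysis): "All data will be analyzed by intention".
- Section 2.8 (Rejection, termination, and shedding criteria): "Patients who receive treatment but not in accordance to the regulations or those who have incomplete data will be excluded".
- Section 3.4 (Compliance): "The researchers will pay close attention to patients’ compliance and exclude patients with poor compliance".
- Section 2.8 again. Voluntary withdrawals, and patients with adverse events who are "not suitable for further treatment will be regarded as part of the attrition", are handled as losses. One group of withdrawals is then brought back: "Patients who withdraw from more than 1/2 courses of treatment due to ineffectiveness will be included in the efficacy analysis".

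The treatment sections supply the context. Under section 3.1.2 the experimental arm "will additionally be treated with the improved sitting Wuqinxi intervention", in four timed sessions a day. Under section 3.1.1 the control arm receives usual ICU treatment and care, with no exercise programme.

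**The concern.** Off-protocol treatment and poor compliance can be seen only once treatment has begun, so these exclusions act after randomisation and are not screening rules. An analysis by intention keeps such patients. The two instructions define different patient sets for every efficacy comparison, and with both in force the set could be chosen after the data are seen.

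The compliance rule raises a second problem. Entry requires clear consciousness and the ability to follow instructions (section 2.7.1). The outcomes include disordered consciousness, delirium and ICU-acquired weakness (section 3.2.1). A Wuqinxi patient who develops one of these may be unable to exercise, may be judged non-compliant, and may then leave the analysis together with the complication. A similar control patient has no exercise sessions to miss. Section 3.6 masks data observers and statisticians, but section 3.4 leaves the exclusion decision to the researchers, who are not described there as masked.

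**Working it through.** **1. The plan's own figure.** Inputs from section 2.4: d = 0.50, "The test level was α = 0.05", power 0.80, attrition up to 20%. A two-sided two-sample t-test needs 63.77, so 64 per group and 128 in total. Inflation: 128 / (1 − 0.20) = 160. The stated size reproduces. The inflation fits an analysis that expects to lose patients, in either arm, down to 64 per group.

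**2. The rules side by side.**

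| Randomised patient | Analysis by intention (3.7) | Sections 2.8 and 3.4 |
|---|---|---|
| Treated off-protocol | kept | excluded |
| Incomplete data | kept | excluded |
| Poor compliance | kept | excluded |
| Withdrew, or stopped for an adverse event | kept | attrition |
| Withdrew for ineffectiveness, more than half of the courses | kept | kept |

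The last row would need no rule under analysis by intention. By stating it, section 2.8 implies that other withdrawals are left out. Its wording is also ambiguous: the half may be the part completed or the part missed.

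**3. What unequal exclusion could do.** The document gives no exclusion rate by arm, so these inputs are assumptions: no true effect; 80 randomised per arm; a continuous outcome with SD 1, higher being worse; correlation ρ of 0.3 or 0.5 between the outcome and the severity that drives exclusion; the sickest fraction q removed (5%, 10% or 20%, that is 4, 8 or 16 of 80); two-sided t-test at 0.05; 40,000 simulated trials per row.

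| ρ | q | Wuqinxi arm only: shift (SD) | Wuqinxi arm only: rejection | Both arms equally: rejection |
|---|---|---|---|---|
| 0.3 | 5% | −0.031 | 5.6% | 5.1% |
| 0.3 | 10% | −0.058 | 6.7% | 5.1% |
| 0.3 | 20% | −0.104 | 9.7% | 5.4% |
| 0.5 | 5% | −0.052 | 6.5% | 5.4% |
| 0.5 | 10% | −0.095 | 9.3% | 5.5% |
| 0.5 | 20% | −0.173 | 18.4% | 5.8% |

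Negative shifts favour Wuqinxi. With equal exclusion the shift is within 0.001 SD of zero.

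A closed form checks the shift: −ρ·φ(z)/(1 − q), where z is the normal quantile at 1 − q. For q = 20%, φ(0.8416) = 0.280 and 0.280/0.80 = 0.350. That gives −0.105 at ρ = 0.3 and −0.175 at ρ = 0.5, in line with the simulation.

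**4. After the fix.** At d = 0.50, power is 0.88 with all 80 per arm analysed and 0.80 with 64, provided non-compliance does not dilute d.

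**The case against.** A reader might infer more: that the sickest Wuqinxi patients drop out of one arm only, so that every outcome looks better than it should. The document does not support this.

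- The off-protocol, incomplete-data, withdrawal and adverse-event rules name no arm. Only the compliance rule plausibly falls mainly on the Wuqinxi arm.
- No section says that excluded patients are sicker.
- The direction can differ by outcome. Early deaths shorten ventilation time, ICU stay and cost, so removing them can make the retained group look worse. Patients extubated or discharged early may also have incomplete sessions or data, and dropping them would count against Wuqinxi.
- Keeping some withdrawals for ineffectiveness partly offsets a bias toward the intervention.
- The 20% in section 2.4 is an upper limit applied to both groups. Placing all of it in one arm is the unfavourable end.

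These points stand, and they limit what can be said about direction and size.

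Two further objections carry less weight. In section 3.4, exclusion may mean ending participation, since the next sentence is about whether a patient can continue. But a patient whose participation ends may have incomplete data, which section 2.8 excludes, and section 2.8 itself speaks of the efficacy analysis. Second, an analysis plan not shown may define the sets. It could choose one rule, but it could not satisfy both while the protocol states both.

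**Conclusion.** The contradiction is certain: the exclusions in sections 2.8 and 3.4 are incompatible with the analysis by intention in section 3.7. This is a wrong rule in the text, not a detail left to another document, and it affects every efficacy comparison, so it must be fixed.

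The bias is a credible risk, not a demonstrated one. It needs exclusions that are both unequal between arms and related to prognosis. Under the stated assumptions, false positives range from close to the nominal 5% up to about 18%. The top value requires 20% exclusion in one arm, none in the other, and a correlation of 0.5. Toward the intervention is the plausible direction, not a certain one.

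**What to change.** 1. State in section 3.7 that the main efficacy analysis includes all randomised patients in the arm assigned, whatever their compliance, adverse events or withdrawal from exercise.
2. Remove the off-protocol, incomplete-data, poor-compliance and half-of-courses rules (sections 2.8 and 3.4) as criteria for that set. The sentence in 2.8 on patients who do not meet the inclusion criteria is a separate matter and can be left alone here.
3. Keep taking complications, ventilation time, ICU stay and cost from the ICU record after a patient stops exercising, unless consent for data use is withdrawn.
4. Handle outcomes still missing by a prespecified method, for example multiple imputation with a sensitivity analysis, instead of exclusion.
5. Keep the compliant set as a labelled per-protocol sensitivity analysis, with compliance defined in advance.

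This changes who is analysed, not when treatment stops. The planned 160 patients stay. The cost is amended wording, a little more data collection and analysis work, and possibly a smaller estimated effect.

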## Interventions

3

### Treatment plan

3.1

#### Control group

3.1.1

The control group will receive standardized comprehensive western medicine treatment (including mechanical ventilation) and routine care in the ICU.

#### Experimental group

3.1.2

The experimental group will receive the same treatment as the control group and will additionally be treated with the improved sitting Wuqinxi intervention.

(1)Establish the standardized flowchart of “improved sitting Wuqinxi”for mechanically ventilated ICU patients(2)There will be 3 groups of tiger opera at 09:00, 6 times in each group; 3 groups of bear play at 13:00, 6 times in each group; 3 groups of bird play at 15:00, 6 times in each group; and 3 groups of deer play at 19:00, 6 times in each group.(3)Establish the risk assessment system

### Observation index

3.2

#### Incidence of ICU mechanical ventilation complications

3.2.1

The ICU consciousness disorder assessment form and delirium scale analysis system will be used to evaluate each patient state of consciousness. The presence of ICU-AW will be judged according to the British Medical Research Council grade 6. The incidence of ventilator-associated pneumonia, pulmonary infarction, and pressure ulcers will also be observed.

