## Introduction

1

With the continuous progress of the theory and technology of mechanical ventilation, its application in the intensive care unit (ICU) has become increasingly common. Patients who need long-term mechanical ventilation in the ICU account for 4% to 13% of the total number of patients.^[1,2]^ Mechanical ventilation has become a powerful tool for the treatment of acute or chronic respiratory failure and other diseases. Thus far, studies on mechanically ventilated patients have mainly focused on in-hospital mortality and short-term physiological endpoints.^[3,4]^ However, surviving critically ill patients often develop persistent long-term physiological and psychological complications.^[5]^

Ventilator dependence is a common phenomenon in mechanically ventilated ICU patients. Previous studies have shown that 39% mechanically ventilated patients have difficulty weaning from mechanical ventilation and that 18% patients have prolonged mechanical ventilation time.^[6]^ Long-term mechanical ventilation leads to various complications, such as ICU-acquired weakness (ICU-AW), dysfunction of the cardiac circulation system, metabolic disorders, and psychological disorders. ICU-AW is a common complication in mechanically ventilated patients. The incidence of ICU-AW can reach up to 33.0% to 82.0% in patients on mechanical ventilation for >4–7 days.^[7,8]^ Complications caused by mechanical ventilation not only prolong the duration of mechanical ventilation and length of ICU stay but also seriously damage patients’ functional recovery.^[9,10]^

Wuqinxi is a traditional Chinese sports healthcare method created by Hua Tuo, an ancient famous doctor. Wuqinxi is based on the theories of yin and yang, 5 elements, Zang Xiang, and meridians. Five birds (deer, ape, bear, bird, and tiger) belong to the 5 elements (wood, fire, soil, gold, and water), which also correspond to the 5 Zang organs (the liver, heart, spleen, lung, and kidney). Wuqinxi has recognized clear disease prevention and health care effects and can regulate the 5 Zang organs.^[11]^

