Long-term bed rest and immobilization lead to serious complications in critically ill patients on mechanical ventilation. Early activity is a very safe and effective strategy for disease prevention and rehabilitation.^[12–14]^ Previous studies have shown the safety and feasibility of early activity in mechanically ventilated ICU patients.^[15–17]^ However, the current unified early activity plan is relatively simple and its clinical efficacy is unclear. The traditional sitting Baduanjin intervention can achieve good clinical effects in patients with sepsis-induced mechanical ventilation.^[18]^ Based on this finding and the clinical characteristics of ICU patients, the traditional sports health care skill Wuqinxi was adapted into the “improved sitting Wuqinxi” intervention for severe patients under the guidance of professional Wuqinxi practitioners. Wuqinxi can reduce the incidence of delirium in mechanically ventilated ICU patients, shorten the duration of mechanical ventilation, and prevent complications and damages secondarily to mechanical ventilation. However, sufficient clinical evidence is needed to confirm its effectiveness. Therefore, our goal of this study will be to evaluatethe efficacy and safety of the improved sitting Wuqinxi intervention in mechanically ventilated ICU patients using a prospective, randomized, controlled, and multicenter clinical study design.

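### Patients who stay too confused or delirious for strength grading may have no ICU-acquired weakness value, and the exclusion of incomplete data could lose them unequally by arm

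*Protocol article*

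**What the plan says.** Section 3.2.1 of the protocol article lists the complications to be counted. On weakness: "The presence of ICU-AW will be judged according to the British Medical Research Council grade 6". Under the same heading: "The ICU consciousness disorder assessment form and delirium scale analysis system will be used to evaluate each patient state of consciousness".

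Three other places bear on who can be graded and who is kept:

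- Section 2.7.1 admits only patients with "Clear consciousness and the ability to act in accordance with instructions". This applies at entry.
- The Introduction states that "Wuqinxi can reduce the incidence of delirium in mechanically ventilated ICU patients", and then adds that evidence is still needed to confirm effectiveness.
- Section 2.8 says that "those who have incomplete data will be excluded", while section 3.7 says "All data will be analyzed by intention".

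The Discussion adds that there is no follow-up once patients are discharged.

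**The concern.** Medical Research Council grading asks the patient to move against resistance on command. That is a property of the named method; the article does not state it. Inclusion criterion 3 secures cooperation at enrolment but not at later gradings. A patient who becomes delirious or loses clear consciousness, and does not recover before leaving the ICU, may never yield a post-randomisation grade.

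Whether ICU-AW can be measured may therefore depend on another outcome of the trial, one that the intervention is expected to change. If ungradable patients are dropped as incomplete, the ICU-AW comparison is confined to patients selected after randomisation, and the selection can differ by arm. Analysing everyone as randomised does not resolve this on its own, because it supplies no value for a patient who could not be graded. If section 2.8 is applied to whole patients, the same people also leave the comparisons of ventilation time, ICU stay and cost.

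**Working it through.** **The plan's own figure.** The point challenges no stated number; only the arm size is used. A two-sided t-test with d = 0.50, α = 0.05 and power 0.80 needs 63.77, so 64 per group. Then 128/(1 − 0.20) = 160, or 80 per arm. The stated figures reproduce.

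**Inputs.** The article gives no delirium rate and no share of patients who stay ungradable, so these are assumptions:

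- Delirium: pC = 0.30 (control), pW = 0.15 (Wuqinxi).
- ICU-AW risk: r1 = 0.82 with delirium, r0 = 0.33 without, the same in both arms (no direct effect on strength). The two values borrow the ends of the range in the Introduction, "The incidence of ICU-AW can reach up to 33.0% to 82.0% in patients on mechanical ventilation for >4–7 days", which is not itself split by delirium.
- u = share of delirious patients never gradable, the same in both arms, varied from 10% to 100%.

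**True difference.** Rate = p·r1 + (1 − p)·r0.

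- Control: 0.30 × 0.82 + 0.70 × 0.33 = 0.477
- Wuqinxi: 0.15 × 0.82 + 0.85 × 0.33 = 0.4035
- Wuqinxi minus control: −7.35 points

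**Difference if the ungradable are excluded.** Number scored = 80(1 − p·u). Observed rate = [p(1 − u)r1 + (1 − p)r0] / (1 − p·u). For u = 0.10:

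- Control: (0.2214 + 0.231)/0.97 = 46.6%
- Wuqinxi: (0.1107 + 0.2805)/0.985 = 39.7%
- Difference: −6.9 points

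| u | Scored, control vs Wuqinxi | Observed difference (true −7.35) |
|---|---|---|
| 10% | 77.6 vs 78.8 | −6.9 |
| 25% | 74 vs 77 | −6.2 |
| 50% | 68 vs 74 | −4.7 |
| 100% | 56 vs 68 | 0.0 |

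**Other assumptions.**

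- Weaker link (ICU-AW 60% with and 40% without delirium), still 30% vs 15%: true −3.0; excluded −2.8 at u = 10% and 0.0 at u = 100%.
- More delirium (50% vs 30%, risks 82% and 33%): true −9.8; excluded −9.6 at u = 10%, and 0.0 at u = 100% with 40 vs 56 scored.
- Delirium 30% in both arms: 56 vs 56 scored at u = 100%, and the difference is unbiased at every u.

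**Does the sign depend on the handling?** Take 30% vs 15% ungradable.

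- ICU-AW 40% among gradable patients in both arms: exclusion gives 0. Scoring the ungradable as not weak gives 0.85 × 0.40 − 0.70 × 0.40 = +6.0 points.
- ICU-AW 40% vs 25% among gradable patients: exclusion gives −15.0. Scored not weak: 21.25% − 28.0% = −6.75. Scored weak: 36.25% − 58.0% = −21.75. All three have the same sign.

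A reversal therefore needs a not-weak coding together with little or no direct effect on strength.

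**The case against.** The strongest reply is that an article gives each complication a line or less. Grading times and the coding of patients who cannot be assessed may sit in Figure 2, which is not shown, or in the full protocol. That stands: their absence here is not held against the plan. The point rests on a rule that is written, namely exclusion for incomplete data, applied to an outcome whose measurability may differ by arm. A schedule alone would not remove that rule.

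A reader might infer that delirious patients cannot be scored and will drop out unequally. The documents do not support this. Nowhere do they say that such patients go ungraded. Delirium can resolve and a patient can be graded later. Unequal loss, with equal gradability among delirious patients, needs both a real delirium difference, which the Introduction treats as still to be confirmed, and patients who stay ungradable throughout. If few do, the bias is negligible (−6.9 against −7.35).

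A reader might also infer that the sign of the ICU-AW result is at the mercy of the sites. That is not supported either. The only written rule is exclusion, which in the illustration shrinks the difference towards zero without reversing it. Coding the ungradable as not weak is nowhere stated, and with a direct strength effect the sign held under all three codings above.

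Finally, the clash between 2.8 and 3.7 touches every outcome and does not need the delirium pathway. True; ICU-AW is where there is a stated reason to expect the losses to be informative.

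**Conclusion.** The concern holds as a conditional risk. ICU-AW depends on cooperation, delirium and consciousness are assessed under the same heading, the trial expects delirium to be lower with Wuqinxi, and section 2.8 would discard patients left without a grade, against section 3.7. If that rule is followed and delirium does differ, ICU-AW data could be lost unequally by arm.

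The size cannot be fixed from the documents. Under 30% vs 15% delirium, ICU-AW 82% and 33%, and no direct strength effect, exclusion leaves between −6.9 and 0.0 of a true −7.35 points as u goes from 10% to 100%. The bias in the difference vanishes if delirium and ICU-AW risks are equal by arm. This warrants a cheap improvement to the wording; it does not show that the ICU-AW comparison must fail.

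**What to change.** 1. In 2.8, state that no randomised patient is excluded because ICU-AW could not be graded, and reconcile the incomplete-data clause with analysis by intention in 3.7.
2. In 3.2.1, state that ICU-AW is graded when the patient passes the consciousness and delirium assessments already planned, with the attempt repeated up to ICU discharge if needed.
3. Report the number never gradable, by arm.
4. Give two bounding analyses in all randomised patients: all ungradable scored weak, and all scored not weak. In the main illustration the gap between them is u(pC − pW): 0.10 × 0.15 = 1.5 points at u = 10% and 15 points at u = 100%. The bounds stay close when few patients are lost. They bracket the truth if ungradable patients are weak equally often in both arms.
5. Keep any composite of ICU-AW or never gradable as a sensitivity analysis only. It counts every ungradable patient as weak, so a delirium effect can appear as a strength effect. With 30% vs 15% ungradable and ICU-AW 40% in gradable and 70% in ungradable patients, the true difference is 0.445 − 0.49 = −4.5 points, while the composite gives 0.49 − 0.58 = −9.0.

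The cost is protocol wording, some repeat bedside grading, and a wider stated range for the ICU-AW result. The consciousness and delirium assessments are already planned.
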